### Outcomes

The primary outcome is *time to clinical stabilization*, defined as the time from randomization to meeting all the criteria.

The primary and secondary outcomes have been provided in Textbox 2.

Primary and secondary outcomes.

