**Primary outcome**
Temperature of 37.8 °C or lessHeart rate of 100 beats per minute or lessRespiratory rate of 24 breaths per minute or lessSystolic blood pressure of 90 mm Hg or higherOxygen saturation of 90% or higher or arterial partial pressure of oxygen of 60 mm Hg or higher on room air

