### Sample Size Calculation

The sample size was based on a previous RCT [16], which reported that the mean time to clinical stabilization (used as a proxy for hospital discharge) in patients with CAP was 3.6 (SD 1.9) days in patients who were in the vitamin C group compared to 4.7 (SD 2.0) days in the placebo group. Using this effect size (1.1 days), a pooled SD of 1.95, a power of 80%, and a 2-sided α of .05, the required sample size is 102 participants (51 per group). To account for an anticipated 20% attrition rate due to loss to follow-up or mortality, we plan to recruit 124 participants (62 per group).

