### Data Collection and Follow-Up

Clinical data will be collected daily during hospitalization. Follow-up assessments will be conducted at 30 days and 6 months after randomization via telephone interview. Data will be recorded using secure electronic case report forms. The schedule of enrollment, interventions, and outcome assessments is summarized in Table 1.

**Table 1 table1:** Schedule of enrollment, interventions, and assessments for the Vitamin C in Community-Acquired Pneumonia trial.

	Screening and baseline	Day 0—randomization	Days 1-7—hospital phase	Day 30—follow-up	Month 6—follow-up
Eligibility assessment	✓				
Informed consent	✓				
Randomization		✓			
Vitamin C or placebo administration		✓	✓	✓	
Clinical observations (vital signs)	✓	✓	✓^a^		
CAP^b^ symptom assessment	✓		✓	✓	
Early clinical response assessment			✓^c^		
Inflammatory biomarkers (CRP^d^ and PCT^e^)	✓		✓^f^		
Hospital outcomes (ICU^g^ admission, ventilation, and vasopressor use)			✓		
Length of stay			✓		
Adverse event monitoring		✓	✓	✓	✓
Hospital readmission				✓	
Health-related quality of life (EQ-5D-5L)				✓	✓
Mortality assessment			✓	✓	✓

^a^Daily during hospitalization (days 1-7).

^b^CAP: community-acquired pneumonia.

^c^Assessed on days 3-5.

^d^CRP: C-reactive protein.

^e^PCT: procalcitonin.

^f^Measured on day 7 or at discharge (whichever occurs first).

^g^ICU: intensive care unit.

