#### Primary Outcome Analysis

The primary outcome, time to clinical stabilization, will be analyzed using a Cox proportional hazard regression model with treatment group as the primary exposure. Results will be reported as hazard ratios with 95% CIs accounting for censoring. The proportional hazard assumption will be assessed using Schoenfeld residuals and log-log survival plots.

The primary Cox model will be adjusted for the following prespecified baseline covariates selected a priori based on clinical relevance: age, sex, baseline pneumonia severity (confusion, uremia, respiratory rate, blood pressure, and age ≥65 years [CURB-65] score), baseline C-reactive protein concentration, and key comorbidities (eg, chronic cardiovascular, respiratory, or metabolic conditions). These covariates were selected to account for potential confounding effects of multimorbidity on clinical recovery. Randomization is stratified by pneumonia severity to ensure balance between groups across this critical prognostic variable.

As a sensitivity analysis, time to clinical stabilization will also be assessed using restricted mean survival time over a clinically relevant time horizon, providing an absolute measure of treatment effect that does not rely on the proportional hazard assumption.

An additional sensitivity analysis will be performed using an independent-sample *t* test (2-sided) or linear regression depending on the distribution of the outcome. The linear regression model will allow for adjustment for the same prespecified covariates, and results will be reported as mean differences with 95% CIs.

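### Eligible patients whose usual state lies outside a stability limit can go home recovered with no recordable primary event, and enter the analysis as non-events unless a rule says otherwise

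*Protocol article*

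**What the plan says.** Under Outcomes, the primary endpoint is "defined as the time from randomization to meeting all the criteria". Textbox 2 lists five criteria: temperature, heart rate (100 or less), respiratory rate, systolic pressure and oxygenation. All are absolute values. The oxygenation criterion accepts a saturation of 90% or higher, or "arterial partial pressure of oxygen of 60 mm Hg or higher on room air". No criterion has an alternative for a patient whose usual value lies outside it.

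Under Data Collection and Follow-Up, "Clinical data will be collected daily during hospitalization", and footnote a of Table 1 narrows the vital signs to "Daily during hospitalization (days 1-7". After that, "Follow-up assessments will be conducted at 30 days and 6 months after randomization via telephone interview". Table 1 has no vital signs at day 30 or month 6.

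Textbox 1 excludes severe renal impairment, nephrolithiasis and several other conditions, but not long-term oxygen, chronic hypoxemia or a habitually fast heart rate. Chronic cardiovascular and respiratory disease are expected, because Primary Outcome Analysis names them as examples of the comorbidities used for adjustment. The same section gives the analysis as a Cox model and says "Results will be reported as hazard ratios with 95% CIs accounting for censoring". It states neither a censoring time nor how discharge before the event is counted. The sensitivity analyses are restricted mean survival time and a t test or linear regression.

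**The concern.** A patient who normally uses oxygen at home, or whose usual heart rate exceeds 100, may be discharged back at the usual level without having met all five limits. The limits cannot be measured by telephone, so no event can be recorded later. The primary analysis includes all randomized patients, so this patient enters as a non-event. The last usable observation is at or before discharge, which makes censoring there the likely default.

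That censoring would not be independent of the outcome, because the patient left through having recovered. Restricted mean survival time drops the proportional hazards assumption but still needs independent censoring. The t test and linear regression need a time for every patient, and these patients have none. The stated sensitivity analyses therefore do not cover the problem. At stake are recoveries missing from the event count, and a primary estimate that depends on a coding choice the text leaves open.

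**Working it through.** **Reproducing the plan's sample size.** Inputs from Sample Size Calculation: difference 1.1 days, SD 1.95, power 80%, two-sided alpha 0.05. The normal formula gives 2 × (1.960 + 0.842)² × 1.95² / 1.1² = 49.3, so 50 per group. The t-based solution is 50.3, so 51 per group and 102 in total, as stated. Then 51 × 1.2 = 61.2, rounded up to 62 per group, gives 124. This calculation compares means, so it gives every analyzed patient a time. The 20% allowance is for loss to follow-up or mortality, not for alive discharge without the event.

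**Simulation set-up.** The means and SDs are the protocol's: 3.6 (1.9) days on vitamin C and 4.7 (2.0) on placebo. Assumptions: gamma-shaped times, 51 per arm, unadjusted Cox model, observation ending at day 7, discharge at the moment of recovery, and a share q of patients who never meet all the limits. There were 3,000 runs per scenario. A hazard ratio (HR) above 1 means faster stabilization on vitamin C.

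Under the gamma shape, 12.7% of placebo and 5.7% of vitamin C patients stabilize after day 7. Expected events with q = 0 are therefore 51 × 0.873 + 51 × 0.943 = 92.6; the simulation gave about the same.

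**Equal share in both arms:**

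| q | Discharge counted as event: HR, power | Censored at discharge: HR, power, events | Non-event to day 7: HR, power |
|---|---|---|---|
| 5% | 1.70, 70.9% | 1.70, 68.1%, 87.9 | 1.59, 56.5% |
| 10% | 1.70, 71.6% | 1.69, 64.8%, 83.4 | 1.50, 44.5% |
| 15% | 1.69, 70.0% | 1.70, 62.3%, 78.8 | 1.44, 36.5% |
| 20% | 1.70, 70.8% | 1.71, 60.7%, 74.1 | 1.40, 29.5% |

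The loss from censoring is 70.9 − 68.1 = 2.8 points at 5% and 70.8 − 60.7 = 10.1 points at 20%. The simulation error of one such difference is about √(2 × 0.7 × 0.3 / 3000) = 1.2 points, so the 5% figure is imprecise. The 71% reference differs from the planned 80% because it is a Cox analysis of gamma times stopped at day 7. Only the differences matter here.

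**Why the HR hardly moves.** If the same share is censored at recovery in each arm, the observed event hazard is (1 − q) times the true one in both, and the factor cancels. Events fall by the same factor: 92.6 × 0.8 = 74.1 at 20%. A hand check uses power ≈ Φ(√d / 2 × ln HR − 1.96) with ln 1.70 = 0.531. With d = 92.6 it gives Φ(0.59) = 72%; with d = 74.1 it gives Φ(0.32) = 63%. In this set-up, fewer events explain nearly all of the loss.

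**Variant.** With discharge 0.3 to 1.5 days after recovery and no stop at day 7, 4,000 runs gave 61% censored against 68% as an event at q = 10%, and 53% against 67% at q = 20%. Leaving these patients out altogether gave 64% and 60%. Here about half the loss is simply fewer events. At q = 5% the loss is again about 3 points.

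**Unequal shares, no true effect (15% placebo, 5% vitamin C).** The same reasoning predicts HR = 0.95 / 0.85 = 1.12 under censoring. The simulation gave 1.11 with a type I error of 7.6%. Holding these patients as non-events to day 7 gave 1.25 and 16.9%. Counting discharge as the event gave 1.00 (1.005 before rounding) and 5.1%.

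**The case against.** The strongest objection is that the article states no rule for discharge before the event. A reader might infer that these patients are censored at discharge, but the text does not say so. Censoring rules commonly belong in the analysis plan, which is not shown. This stands: the absence of a rule is not itself the finding. What remains is the endpoint wording, which is fixed here and makes these patients non-events under any rule that applies it literally. An analysis plan also cannot recover a usual oxygen or heart-rate value that was never collected.

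Second, the room-air qualifier may attach only to arterial pressure. A patient saturating at 90% or more on oxygen would then meet the criterion, and the long-term oxygen example falls away. This stands as a condition on that example. The heart-rate example is unaffected, and the wording still needs to be made clear.

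Third, a reader might infer that more recoveries would be lost in the vitamin C arm if treatment brings discharge forward. The documents do not support this. The traits in question precede randomization, so they are balanced in expectation, and the power figures assume equal shares.

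Fourth, hospital length of stay is already a secondary outcome with a Cox analysis. That analysis counts discharge for everyone. It does not keep stabilization as the event where it was observed, so it does not replace the sensitivity analysis proposed here. A separate request for discharge-day vital signs is not needed up to day 7, because daily collection already covers it.

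**Conclusion.** The point holds as a weakness of the endpoint definition, worth correcting but limited in size. As worded, some eligible patients can recover and go home without a recordable event, and none of the stated analyses repairs that.

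If they are censored at discharge, the power loss is about 3 to 10 points for an affected share of 5% to 20% equal in both arms, with the HR almost unchanged. Some or nearly all of that loss is simply fewer events, depending on how soon discharge follows recovery. The result rests on an unknown share, an assumed gamma shape and an assumed stop at day 7; a share below 5% would cost less. A biased HR, about 1.11 under no effect, arises only if the shares differ by arm, and nothing in the document suggests that they will. The choice of rule matters more: at a 10% share the HR is 1.69 if these patients are censored at discharge and 1.50 if they are held as non-events to day 7.

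**What to change.** 1. In Textbox 2, state whether the room-air qualifier applies to saturation as well as to arterial pressure. For a participant with a documented pre-admission value outside a limit, count return to that pre-admission level as meeting the criterion. This is for endpoint scoring only and does not bear on treatment or discharge decisions. It needs one baseline field, if the case report form does not already hold it.
2. Prespecify a sensitivity analysis in which alive discharge to usual residence before the event (not for palliative care, not a transfer) counts as stabilization at the time of discharge.
3. Where the stay exceeds day 7, continue the daily vital signs until discharge, so that Table 1 agrees with the text on daily collection.

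The cost is slight extra form work and one extra model run. The baseline field is best added before recruitment starts.

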### Study Aim and Hypotheses

The primary aim of the VitCAP trial is to determine whether high-dose oral vitamin C (sodium ascorbate) administered during hospitalization and continued for 30 days after discharge improves clinical recovery in adults hospitalized with CAP when compared with placebo alongside standard care. The primary hypothesis is that vitamin C supplementation will reduce the time to clinical stabilization compared with placebo.

Secondary hypotheses are that vitamin C supplementation will (1) improve early clinical response; (2) reduce hospital LOS; (3) decrease the need for intensive care, ventilatory support, or vasopressors; (4) reduce mortality and hospital readmission; (5) improve patient-reported symptom burden and HRQOL; and (6) reduce systemic inflammatory biomarkers, including C-reactive protein and procalcitonin.

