**Secondary outcomes**
Early clinical response [22], defined as improvement in at least 2 of 4 specific symptoms (chest pain, cough, sputum production, and dyspnea) without any symptom worsening 3 to 5 days after randomizationImprovement in community-acquired pneumonia–related symptoms at 30 days from the day of randomization, measured using the 18-item community-acquired pneumonia symptom questionnaire [23] (range 0-90)Intensive care unit admissionRequirement for noninvasive or invasive mechanical ventilationVasopressor useLength of hospital stayAll-cause mortality at 30 days and 6 months30-day hospital readmissionHealth-related quality of life at 1 and 6 months using the EQ-5D-5L [24]Inflammatory biomarkers (C-reactive protein and procalcitonin) measured at baseline and day 7 or discharge

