#### Secondary Outcome Analysis

Hospital LOS will be analyzed similarly using *t* tests or linear regression, with Cox regression as a secondary analysis. Although LOS data are likely to be nonnormally distributed, the *t* test and linear regression models are considered robust due to the sample size (n>30 per group), which satisfies the conditions of the central limit theorem.

HRQOL at 1 and 6 months will be assessed using linear mixed-effects models to account for repeated measures, and binary outcomes (eg, ICU admission and in-hospital mortality) will be compared using logistic regression. Biomarkers will be analyzed as change from baseline with adjustment for time from randomization to follow-up sampling. Linear regression and mixed-effects models incorporating time as a covariate will be used, with sensitivity analyses restricted to samples collected within a predefined time window.

Baseline differences between groups in clinical and demographic variables will be assessed using *t* tests, Wilcoxon rank-sum tests, or chi-square or Fisher exact tests as appropriate. Missing data will be addressed using multiple imputation, and additional sensitivity analyses will be performed in subgroups, such as patients with moderate to severe pneumonia (CURB-65 score≥2).

Statistical significance for all outcomes will be determined using a 2-sided type I error rate of α=.05. All analyses will be performed using Stata (version 19.0; StataCorp).

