#### Subgroup Analyses

Prespecified subgroup analyses will examine the effects of vitamin C in clinically important subgroups, including older participants (aged <65 years vs ≥65 years), participants with frailty (Clinical Frailty Scale score of 1-5 vs ≥5), participants with moderate to severe pneumonia (CURB-65 score of <2 vs ≥2), and participants with higher multimorbidity burden (Charlson Comorbidity Index of <3 vs ≥3). Separate regression models will be performed for each subgroup.

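### EQ-5D-5L has no baseline or pre-illness measurement, so the quality-of-life comparison cannot be adjusted for prior quality of life and loses precision

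*Protocol article*

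**What the plan says.** Three places in the protocol article agree on when HRQOL is measured.

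- **Data Collection and Follow-Up, Table 1.** The row that begins "Health-related quality of life (EQ-5D-5L" is ticked under day 30 and month 6. The cells for screening and baseline, day 0 and the hospital phase are empty. The text above the table adds: "Follow-up assessments will be conducted at 30 days and 6 months after randomization via telephone interview".
- **Outcomes, Textbox 2.** EQ-5D-5L is listed at 1 and 6 months.
- **Secondary Outcome Analysis.** "HRQOL at 1 and 6 months will be assessed using linear mixed-effects models to account for repeated measures". No baseline or recalled pre-illness value appears here or anywhere else in the article.

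Other measures are handled differently. Table 1 ticks the CAP symptom assessment and CRP/procalcitonin at screening and baseline. Textbox 2 lists the biomarkers as "measured at baseline and day 7 or discharge", and the analysis text uses that baseline: "Biomarkers will be analyzed as change from baseline with adjustment for time from randomization to follow-up sampling".

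HRQOL is part of a stated secondary hypothesis, that vitamin C will "improve patient-reported symptom burden and HRQOL" (Study Aim and Hypotheses).

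**The concern.** How a person rates their health one or six months after pneumonia is likely to depend partly on how they rated it before. This trial enrolls adults of any age from 18, under general medicine, respiratory or intensive care teams. Frailty and comorbidity vary enough to define subgroups, for example "Charlson Comorbidity Index of <3 vs ≥3". Prior HRQOL is therefore likely to differ widely between participants.

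Randomization is stratified by pneumonia severity only, so nothing in the design balances prior HRQOL. Without a starting value, two things follow. The part of the follow-up variance that prior HRQOL would explain stays in the error term, except where other covariates capture it. And if the arms happen to differ in prior HRQOL, the trial can neither show this nor adjust for it directly.

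The gap lies in data collection, so it is not a detail that can wait for the analysis plan. Each participant enrolled without the measurement is a permanent loss for this purpose.

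**Working it through.** **Inputs from the protocol article (Sample Size Calculation).** Difference 1.1 days, pooled SD 1.95, power 80%, two-sided alpha 0.05; 51 per group required, 62 per group recruited, 20% attrition expected.

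**The plan's own figure.** n per group = 2 × (1.960 + 0.842)² × 1.95² / 1.1² = 49.3, so 50 by the normal approximation. The t-based solution is 50.3, rounded up to 51 per group, or 102 in total, as stated. This figure concerns time to clinical stabilization and does not depend on EQ-5D-5L. The article gives no SD, target difference or power for HRQOL, so the results below are in SD units.

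**Assumptions.** 51 evaluable per arm at the HRQOL assessment (62 × 0.8 = 49.6 gives nearly the same answer). The correlation r between baseline and follow-up EQ-5D-5L is not in the document and is set at 0.2, 0.4 and 0.6. The comparison is at one follow-up time, against a model with no covariates.

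**Chance imbalance in prior HRQOL.** Standard error of the between-arm difference = √(2/51) = 0.198 SD; 95% range ±1.96 × 0.198 = ±0.39 SD. With all 62 per arm it is √(2/62) = 0.180 SD, range ±0.35 SD.

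**Precision gained by adjusting for a baseline.** Residual variance is multiplied by 1 − r². The equivalent gain in participants is 1/(1 − r²) − 1. The minimum detectable difference at 80% power is (1.960 + 0.842) × √(2/51) × √(1 − r²).

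| r | Fall in variance (r²) | Equivalent extra participants | Minimum detectable difference |
|---|---|---|---|
| no baseline | – | – | 0.55 SD |
| 0.2 | 4% | 1/0.96 − 1 = 4% | 0.54 SD |
| 0.4 | 16% | 1/0.84 − 1 = 19% | 0.51 SD |
| 0.6 | 36% | 1/0.64 − 1 = 56% | 0.44 SD |

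The imbalance and the lost precision are the same cost seen in two ways and should not be added together. The confidence interval of an analysis without the baseline already allows for chance imbalance; it is simply wider than it need be.

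**The case against.** The strongest reply is that nothing here is an error. The outcome list, schedule and analysis agree with one another. A mixed model on two post-randomization values gives a valid randomized comparison. HRQOL is one of many secondary outcomes and plays no part in the sample size. All of this stands and sets the grade: this is a worthwhile improvement, not a defect in validity.

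A reader might also infer more than the document supports, in four ways.

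- **That the HRQOL comparison is biased.** It is not. Randomization makes the arms comparable on average, and the loss is in precision.
- **That the HRQOL model is unadjusted, or ignores frailty and comorbidity.** The article says only that HRQOL "will be assessed using linear mixed-effects models to account for repeated measures". A condensed article commonly leaves the covariates of a secondary model to the analysis plan, so silence does not show that there are none.
- **That imbalance in prior health cannot be corrected at all.** Age, severity, frailty and comorbidity could be entered and would correct part of it. Only adjustment for prior HRQOL itself is ruled out.
- **That the 18-item symptom questionnaire is already given at baseline, leaving only a trivial addition.** Table 1 ticks a CAP symptom assessment at baseline without naming the instrument. Textbox 2 ties the 18-item questionnaire to the 30-day outcome, and early clinical response uses four separate symptoms.

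Two practical objections also stand. EQ-5D-5L answered during acute pneumonia does not measure usual health and may correlate weakly with follow-up, which is why recall of the pre-illness state is preferable. And some participants will be in intensive care or enrolled through a representative, so some baselines will be proxy-reported or missing.

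**Conclusion.** The point holds as a matter of efficiency. The schedule leaves out a baseline for EQ-5D-5L in all three places where it could appear, so adjustment for prior HRQOL is impossible however the analysis plan is written.

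The size of the loss is uncertain. It runs from negligible (4% of residual variance at an assumed correlation of 0.2) to substantial (36% at 0.6). These figures compare adjustment for baseline with an unadjusted model at a single follow-up time. If age, frailty and comorbidity are in the model as well, the further gain from the baseline would be smaller. The chance imbalance that would go unseen has a standard error of about 0.20 SD with 51 per arm. Neither the primary outcome nor the stated sample size is affected.

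**What to change.** Before recruitment starts:

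1. Tick EQ-5D-5L in the screening and baseline column of Table 1, preferably worded as recall of the usual state before this illness.
2. Allow proxy completion where a representative gives consent, and record who answered.
3. Enter the baseline value as a covariate in the HRQOL mixed model, together with the randomization stratum for severity. State how missing baselines are handled; the article already plans multiple imputation.

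The cost is a few minutes per participant at an assessment that already takes place, one eCRF page, and some proxy-reported or missing baselines. No extra visit or enrollment is needed.
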